#### Patient-reported functional outcomes

Functional status will be evaluated by means of DASH questionnaire (validated for the Portuguese language) at the following intervals: two, six, eight, twelve and twenty-four weeks after fracture reduction [28]. The DASH was developed as an instrument for patients with upper-extremity injuries. The survey contains 30 questions related to the function of the hand, wrist, elbow, and shoulder based on the conditions to do certain activities in the past week, so the evaluations refer only after the beginning of the immobilization.

### Secondary outcomes

Patient Rated Wrist Evaluation – PRWE; [29] Pain (VAS - Visual Analogue Pain Scale); [30, 31] Objective functional evaluation (goniometry and dynamometry); and rate of complications and failures.

The PRWE score (validated for the Portuguese language) will be obtained at eight, twelve and twenty-four weeks. The PRWE contains 15 items that are specific to determining the degree of musculoskeletal disability related to the wrist [29].

Pain in the wrist, elbow and shoulder will be measured separately in all visits at one, two, three, four, six, eight, twelve and twenty-four weeks after fracture reduction by the Visual Analogue Pain Scale (VAS). This is a unidimensional measure of pain intensity, which has been widely used in diverse adult populations [30]. Pain in VAS is a continuous scale comprised of a horizontal line of 10 cm (100 mm) in length, anchored by two verbal descriptors, one for each symptom extreme by “no pain” (score of 0) and “pain as bad as it could be” or “worst imaginable pain” (score of 100). Participants are asked to report pain intensity in the last 24 h. The respondent is asked to place a line perpendicular to the VAS line at the point that represents their pain intensity. Using a ruler, the score is determined by measuring the distance (mm) on the 100 mm line between the “no pain” anchor and the patient’s mark, providing a range of scores from 0 to 100 [31].

#### Objective functional evaluation

Arcs of motion will be measurement for the wrist, and a goniometer will be employed to measure wrist flexion, extension, ulnar deviation, radial deviation and pronosupination at the six, eight, twelve and twenty-four week follow up visit. The flexion–extension of the elbow will be measurement at six, eight, twelve and twenty-four week follow-up visit.

Palmar grip strength with a digital dynamometer (Jamar Plus - Hand Dynamometer), at the following moments of treatment evolution: eight, twelve and twenty-four week follow-up visit.

#### Complications

Any clinical situation requiring treatment (clinical or surgical procedure) not provided in the protocol will be considered as a complication. All complications will be recorded for further stratification into major and minor complications.

In cases where there is loss of reduction, patients will be informed and surgical treatment indicated.

#### Statistical methods

Descriptive data will be exposed as means or proportions followed by standard deviations or 95% confidence intervals. As a method to confirm the effectiveness of the randomization, baseline data will be compared in the two groups of comparison. To ensure the normal distribution of data, we will use visual analysis and Shapiro-wilk test.

For comparison between proportions, we will consider Pearson’s chi-square test. For continuous data, we will use Student T test. Intra-group comparison (1, 2, 3, 4, 6, 8, 12 and 24 weeks) will be analyzed by paired Student T test or Wilcoxon (if data is not normally distributed). We will consider as significant when alpha < 0,05. To analyze the occurrence of complication after treatment, we intend to perform survival analysis associated with Kaplan-Meier curves, if we find greater than 20% complication in any of the comparison groups. All statistical analysis will be performed following intention to treat principle. Statistical advisors will be blinded to the treatment groups as an effort to decrease bias.

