#### Sample size calculation

Based on data derived from one recent randomized clinical trial on the subject [32]. We considered as relevant differences on DASH scores (clinically relevant) when scores are greater than 10 points and standard deviation 15 points [33]. To detect this difference (Student T-test) and statistical power of 95% resulted in a 58 patient sample size per group. We considered an extra 10% for balancing follow up losses. Thus, our inclusion target will be 64 patients per group. We considered the test as bicaudal.

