Our study has several strengths and limitations. Weekly assessments increase the chance of follow-up loss, however a strict control will be adopted. The study presents limitations because the database was constructed based on measurements of X-ray films calculated manually with goniometer and pen, which may imply in unmeasured tolerance limits. To minimize this, the measurements were performed by two senior researchers independently at different times. All patients in this study will be users of the public health system, many of them may have difficulty responding to self-reported questionnaires. A trained assistant will be available in these cases. Another important point to consider is the work compensation in some patients who want secondary gains, which can influence the information collected.

The results from this randomized clinical trial study are expected to be published in december of 2019. We hope that the study results will provide an answer as to which is the best conservative treatment method for DRF.

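### The course over time is tested only within each arm, which does not compare above-elbow with below-elbow casting; arm claims should rest on between-arm contrasts, best taken from one mixed model per continuous outcome.

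*Protocol article*

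**What the plan says.** All of the relevant analysis text is in the protocol article, Statistical methods.

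- Between arms, continuous outcomes: "For continuous data, we will use Student T test". No visit is named there, and no repeated-measures method.
- Over time: "Intra-group comparison (1, 2, 3, 4, 6, 8, 12 and 24 weeks) will be analyzed by paired Student T test or Wilcoxon". Wilcoxon is kept for data that are not normally distributed.
- Significance: "We will consider as significant when alpha < 0,05".
- Analysis set: "All statistical analysis will be performed following intention to treat principle".

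The Discussion expects some attrition ("Weekly assessments increase the chance of follow-up loss") and adds that follow-up will be strictly controlled. The Sample size calculation allows 10% for losses.

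Table 1 schedules radiographs and VAS at eight visits, DASH at five, range of motion at four, and PRWE and grip at three. The Aim and the hypothesis in the Background are between-arm and set at six months. The abstract's Discussion also promises a comparison of function between casts while they are worn, and the main Discussion presents DASH at 2 and 6 weeks as a means of comparing the groups.

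**The concern.** The trial asks between-arm questions, at six months and during immobilisation. The AE arm also changes to below-elbow immobilisation after 4 weeks (Method for closed reduction and immobilization), so the contrast between arms may itself change over the visits. Yet the only analysis that links visits looks inside each arm.

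A within-arm change mixes the natural course of the fracture with any effect of the cast, and randomisation does not protect it. The listed visits start after treatment has begun, so these are not even changes from a pre-treatment value. The risk is a report that one arm changed significantly and the other did not, read as a difference between casts. A second cost is many P values that bear on no stated objective.

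Separate between-arm t-tests do compare the arms, but each uses one visit and discards what the other visits say about the same patient.

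**Working it through.** **1. The plan's own figure.** The Sample size calculation gives "scores are greater than 10 points and standard deviation 15 points" and "statistical power of 95% resulted in a 58 patient sample size per group", and the test is two-sided ("We considered the test as bicaudal"). Normal approximation: n = 2 × (1.960 + 1.645)² × 15² / 10² = 58.5, so 59 per group. The exact t calculation gives 59.5, so 60. Both are within two patients of 58, and 58 × 1.10 = 63.8, rounded to 64. The sample size is not in dispute. It is built on a single between-arm t-test, not on any within-arm test.

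**2. How many within-arm tests the wording could generate.** The protocol lists visits but not which pairs will be compared, so only a range can be given.

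- Five radiographic parameters are continuous: radial height, radial inclination, volar tilt, ulnar variance, and step-off or gap. Carpal alignment is judged by whether two lines intersect, and malalignment is either present or absent, so it is not counted.
- All visit pairs: 8 × 7 / 2 = 28 per parameter and arm; 28 × 5 × 2 = 280.
- Each later visit against the first: 7 × 5 × 2 = 70.
- DASH, five visits: all pairs 10 × 2 = 20; later against first 4 × 2 = 8.

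**3. How often identical arms would look different.** If the true change is the same in both arms and each independent within-arm test has power p, exactly one is significant with probability 2p(1-p).

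- p = 0.5: 2 × 0.5 × 0.5 = 0.50, the maximum.
- p = 0.8: 2 × 0.8 × 0.2 = 0.32.
- p = 0.999: 2 × 0.999 × 0.001 = 0.002.

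The protocol gives no within-arm power, so p must be assumed. Take n = 58 per arm and SD 15 (both from the protocol), with an assumed between-visit correlation r. The SD of a within-patient change is 15 × √(2(1-r)), which is 15 when r = 0.5. Simulated discordance (10,000 trials per setting):

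| Assumed true DASH change in both arms | r = 0.3 | r = 0.5 | r = 0.7 | r = 0.9 |
|---|---|---|---|---|
| 3 points | 37% | 44% | 50% | 16% |
| 4 points | 48% | 50% | 40% | 1% |
| 5 points | 49% | 42% | 19% | 0% |

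For a 10-point change with r = 0.5, the standardised mean change is (10/15) × √58 = 5.08. Power is then about 99.9% and discordance about 0.2%.

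Discordance is therefore common for small or moderate changes and negligible for large ones.

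**4. Patients used, if nothing is imputed.** The protocol gives no missed-visit rate by visit. Assume independent missingness and 64 patients per arm.

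- 5% missed per visit: single-visit t-test 64 × 0.95 = 61; paired test 64 × 0.95² = 58.
- 10% missed per visit: 64 × 0.90 = 58; 64 × 0.90² = 52.

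A mixed model uses every observed value from every patient seen at least once.

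**The case against.** The strongest reply is that the stated aim is already served. It is set at six months, a two-sample t-test at 24 weeks is a valid randomised comparison, and the sample size uses that test. T-tests at 2 and 6 weeks can also compare function in the cast. No objective explicitly asks whether the two courses differ, and with few missed visits a mixed model would give nearly the same week-24 answer. All of this stands, and it limits the point to the longitudinal analysis.

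Several stronger readings are tempting, but the protocol does not support them:

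- *That patients with missed visits will be dropped, against the intention-to-treat statement.* The protocol does not say so. A t-test can be run on imputed data, and missing-data handling is commonly left to a fuller document. Use of observed patients only is an inference.
- *That 336 radiographic tests are planned.* That figure (28 × 6 × 2) treats carpal alignment as continuous and assumes every visit pair is tested.
- *That both arms will improve, so the tests are empty.* This suits DASH and pain. Radiographic parameters are followed to see whether reduction is held or lost, and a within-arm description of drift has some use there.
- *That discordant results should be expected 32% or 50% of the time.* Those values follow from chosen powers of 80% and 50%.
- *That arm differences will be claimed from arm-specific P values.* The protocol nowhere says this; it only leaves the way open.

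The mixed model also has limits. It omits patients with no observed value. An unstructured covariance over eight visits needs 8 × 9 / 2 = 36 parameters from at most 128 patients, so a fallback is needed.

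**Conclusion.** The point holds for the analysis over time. The protocol tests the course of continuous outcomes only within arms, and those tests give no AE-versus-BE comparison. Differing significance between arms is not evidence of an arm difference: under identical arms it occurs with probability 2p(1-p), from near zero up to 50% depending on an unstated power. The within-arm radiographic tests number between 70 and 280 under the two visit-pair schemes considered.

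Between-arm t-tests at a given visit, including 24 weeks, remain valid. Their weakness is that they ignore the correlation between visits and, if nothing is imputed, use only patients observed at that visit. The correlations, changes and missed-visit rates used above are assumptions. The statement that the within-arm tests do not compare the arms depends on none of them. This is a worthwhile, inexpensive improvement, not a defect that invalidates the six-month comparison.

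**What to change.** 1. Delete the intra-group tests, or label them descriptive, and state that every claim about AE versus BE rests on a between-arm contrast.
2. For DASH, PRWE, VAS, range of motion, grip and the five continuous radiographic parameters, fit one linear mixed model per outcome with arm, visit and arm-by-visit terms. Include all randomised patients with at least one observed value.
3. Use an unstructured covariance, and prespecify a simpler structure in case the model does not converge.
4. Report the week-24 arm contrast with its 95% CI as the main result, matching the six-month aim. Report the earlier-visit contrasts and the arm-by-visit term as supportive.

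**Cost.** Revised analysis wording and modest programming; no new data, visits or patients. The model assumes that missing values are missing at random, and this should be stated. With few missed visits, the week-24 estimate will be close to the t-test result.

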#### Randomization and masking

Patients will be randomly assigned using randomization software (available at: http://www.randomizer.org). The allocation of patients in the AE or BE groups will be performed using opaque envelopes numbered on their outer face with consecutive numbers (concealment). Additionally, the envelope will be opened only in the operating room after verification of fracture reducibility and the procedure will be delegated to a person who is not directly connected to the study.

#### Sample size calculation

Based on data derived from one recent randomized clinical trial on the subject [32]. We considered as relevant differences on DASH scores (clinically relevant) when scores are greater than 10 points and standard deviation 15 points [33]. To detect this difference (Student T-test) and statistical power of 95% resulted in a 58 patient sample size per group. We considered an extra 10% for balancing follow up losses. Thus, our inclusion target will be 64 patients per group. We considered the test as bicaudal.

## Discussion

This publication presents a randomized clinical trial of the non-operative treatment of DRF. Casts may be applied either “above elbow” or “below elbow”, depending on the particular type of injury and physician preference. Often, the plaster may extend above the elbow to help provide additional stability and neutralize the extensive forces that can be generated by natural movements of the arm and forearm. Above-elbow immobilization is the conservative treatment used by most of the Brazilian orthopedic surgeons (74%) [34].

Short arm immobilization has been used by many orthopedic surgeons around the world, who claimed equally beneficial results [8, 13]. Hence, controversy still persists regarding the length of the immobilization for the treatment of DRF [4, 5].

The value of the study includes all participants will be reduced in the main operating room under general intravenous anesthesia and with the aid of radioscopy which will allow better control of the pain and maximum quality in the reduction. All reductions and immobilizations will be performed by a single researcher, specialist in hand surgery. The follow up during the immobilization period will be weekly, with radiographic documentation, which allows the early identification of the reduction loss. This is the only trial to apply DASH questionnaire at the beginning and end of immobilization period (2 and 6 weeks) to compare the groups. Pain in the wrist, elbow and shoulder will be measured separately in all visits to verify the influence of immobilization on the elbow and shoulder joints. Adults of all ages will be evaluated, it is known that the DRF in the elderly has different behavior and prognosis when compared to the young [35–38]. Randomization will equalize the distribution homogeneously between the groups, allowing the sample to be faithful to the population.

Our study has several strengths and limitations. Weekly assessments increase the chance of follow-up loss, however a strict control will be adopted. The study presents limitations because the database was constructed based on measurements of X-ray films calculated manually with goniometer and pen, which may imply in unmeasured tolerance limits. To minimize this, the measurements were performed by two senior researchers independently at different times. All patients in this study will be users of the public health system, many of them may have difficulty responding to self-reported questionnaires. A trained assistant will be available in these cases. Another important point to consider is the work compensation in some patients who want secondary gains, which can influence the information collected.

The results from this randomized clinical trial study are expected to be published in december of 2019. We hope that the study results will provide an answer as to which is the best conservative treatment method for DRF.

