### Exclusion criteria

Patients presenting one or more of the following criteria will be excluded from this study:Open fractures, bilateral fracture or associated with tendon or neurovascular lesions.Associated carpal fractures.Marginal fractures or fractures from shearing mechanism.Fractures with palmar deviation (Smith’s fracture).Irreducible fractures (closed method).Prior history of a degenerative or traumatic disorder of the affected or contralateral wrist joint.Systemic diseases or traumatic lesions associated with fracture that restrict the application of methods or the evaluation of results.Cognitive deficit that does not allow the patient to understand the elements of the functional evaluation.Consent Form Refusal.

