### Method for closed reduction and immobilization

The patient will be submitted to the closed reduction of the fracture through a traction and counter-traction technique. Materials needed for application of the two splinting techniques will be available in the operating room. Initially, all patients will receive a short radial splint that will be performed with a 20 cm wide gypsum cut to fit the thumb (Fig. 2a). The splint will be applied to the radial aspect of the wrist covering the volar and dorsal portion of the radius to the elbow. The splint will be moulded with three point fixation as described by Charnley [27]. The three points will be defined after a metal pointer will be placed beside the limb to identify the site of fracture by using the image intensification. Patients randomized to the above-elbow splint will receive a complementation of immobilization with a 15 cm width splint on the ulnar aspect of the forearm that begins at the middle of the forearm and extends into the armpit. The elbow will be immobilized at 90 degrees, and in a neutral position to block pronosupination (Fig. 2b). Cotton tubular mesh, cotton stripes and crepe bandage will be used in both bindings. Regardless of the immobilization adopted, all wrists will be positioned with slight flexion and ulnar deviation. Patients will be encouraged to actively move their fingers and the ipsilateral shoulder.

Patients with above-elbow immobilization will remain for 4 weeks with the splint followed by 2 weeks of below-elbow immobilization. The immobilization will be removed after 6 weeks.

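### No elbow or shoulder pain score is listed before splinting, so the arm comparison cannot be checked or adjusted for prior pain, and effects common to both splints cannot be estimated

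*Protocol article*

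**What the plan says.** The Secondary outcomes section schedules the pain VAS "in all visits at one, two, three, four, six, eight, twelve and twenty-four weeks after fracture reduction", and Table 1 marks the same eight visits. The recall window is short: "Participants are asked to report pain intensity in the last 24 h". The Statistical methods section uses the same time points within arms: "Intra-group comparison (1, 2, 3, 4, 6, 8, 12 and 24 weeks) will be analyzed by paired Student T test" (or Wilcoxon). For continuous data between arms it names the Student t test and no covariate.

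Under Method for closed reduction and immobilization, "Patients with above-elbow immobilization will remain for 4 weeks with the splint followed by 2 weeks of below-elbow immobilization", and all immobilization comes off after six weeks. Week 1 is therefore inside the splint in both arms.

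The Exclusion criteria remove patients with "Prior history of a degenerative or traumatic disorder of the affected or contralateral wrist joint". No matching criterion names the elbow or shoulder. A broader one covers "Systemic diseases or traumatic lesions associated with fracture that restrict the application of methods or the evaluation of results". The Discussion adds that adults of all ages are included.

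The Discussion counts the separate regional scores among the merits of the study: they are to be "measured separately in all visits to verify the influence of immobilization on the elbow and shoulder joints".

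**The concern.** The stated purpose is about what immobilization does to the elbow and shoulder, yet no score is listed from before immobilization. Three consequences follow.

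- **Imbalance cannot be seen.** The planned baseline comparison cannot cover elbow or shoulder pain if none is recorded.
- **Precision is given up.** Patients who already have elbow or shoulder pain add variance to the t test, and no baseline value is available to remove it.
- **Part of the stated purpose is out of reach.** Both arms are splinted for six weeks and there is no unsplinted comparator. The trial estimates the effect of adding elbow immobilization. An effect that both splints share, for example on the shoulder, is not identified.

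At stake is a secondary outcome, but one close to the trial's own hypothesis that above-elbow splinting costs more in complications and function.

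**Working it through.** **1. Arm size.** The article gives no calculation for pain. Its only sample-size figure is for DASH (difference 10, SD 15, two-sided 5%, power 95%): 2 × [15 × (1.960 + 1.645) / 10]² = 58.5 per arm. The stated 58 has power 94.8%, and 58 × 1.10 = 63.8, which gives the stated 64. The figure reproduces within rounding and serves below only as the number of patients per arm.

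**2. Timing.**

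| Item | Where | Content |
|---|---|---|
| First VAS | Table 1; Secondary outcomes | Week 1 |
| Recall | Secondary outcomes | 24 hours |
| Splint, both arms | Method for closed reduction and immobilization | From reduction to week 6 |
| Consent | Initial treatment | Before reduction |
| Envelope opened | Randomization and masking | In the operating room, once reducibility is verified |

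A week-1 score with 24-hour recall cannot reach back before the splint. A score at consent would precede allocation. The article explains the DASH timing by its past-week recall; that reason does not carry over to a 24-hour scale.

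**3. Is the arm comparison biased?** No. A simulation of the unadjusted t test used 58 per arm, 20,000 runs and no true effect. Assumptions, none from the documents: prior pain averaging 30 mm (SD 10) in 10%, 20% or 30% of patients, and SD 20 mm for everything else.

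| Share with prior pain | Added to each arm's mean | Mean arm difference | Type I error | Total SD |
|---|---|---|---|---|
| 10% | 3.0 mm | 0.03 mm | 5.0% | 22.2 mm |
| 20% | 6.0 mm | 0.07 mm | 5.0% | 23.8 mm |
| 30% | 9.0 mm | −0.01 mm | 5.2% | 24.9 mm |

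Prior pain raises the level of each arm and leaves the difference centred on zero.

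**4. Chance imbalance.** With 64 per arm and 30 mm in every affected patient, the 95% range is ±1.96 × 30 × √[2p(1−p)/64]. This gives 3.1, 4.2 and 4.8 mm for p = 0.1, 0.2 and 0.3. It is not an extra error, because the t test's standard error already contains it.

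**5. Precision.** ANCOVA multiplies the residual variance by 1 − r², where r is the assumed correlation between the week-0 and the later score.

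| r | 1 − r² | Variance removed | Equivalent n per arm, 64/(1 − r²) |
|---|---|---|---|
| 0.3 | 0.91 | 9% | 70 |
| 0.5 | 0.75 | 25% | 85 |
| 0.7 | 0.51 | 49% | 125 |

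Under the assumptions of step 3, power for an illustrative 10 mm difference with 58 per arm is 68%, 62% or 58% unadjusted, against 77% if the prior-pain variance were removed in full. Full removal there means r² = 1 − 20²/(total SD)² = 0.19, 0.29 or 0.35, so r of about 0.43 to 0.59, inside the range tabulated.

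**The case against.** A reader might infer that pre-existing pain will be mistaken for an effect of the above-elbow splint. The documents do not support that for the arm comparison: allocation is randomized and concealed, and step 3 shows no bias. The stated Aim is to compare the two casts, and the Discussion sentence follows one about comparing the groups on DASH. Read that way, the influence of immobilization is the arm difference, which the design does identify.

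Nor are the within-arm tests empty. Statistical methods names no reference week, and VAS continues at weeks 8, 12 and 24, after all splints are off. On-splint and off-splint scores can be compared in the same patient, and stable prior pain cancels in that difference. What remains unavailable is the change from before to during splinting.

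Table 1 also starts at week 1 for radiographs, although Initial treatment requires films at presentation, so the table need not list every enrolment measurement. This has some weight. But the running text on pain gives its own full list of visits, also starting at week 1, and the within-arm tests use the same time points.

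The broader exclusion, and the requirement of no other fracture apart from the ulnar styloid, remove some patients with elbow or shoulder problems. They do not plainly cover an earlier local disorder of those joints.

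Finally, a score at consent is taken after the injury and mixes prior with injury-related pain. That is correct and limits its use as a reference. It does not spoil it as a covariate, which needs only to precede allocation and predict the outcome.

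**Conclusion.** The point holds as a minor improvement. The randomized contrast in elbow and shoulder pain is valid as planned, with type I error near 5%. It cannot be checked for baseline imbalance or adjusted for pre-splint pain, and the schedule cannot estimate a before-to-during change or an effect shared by both splints. The Discussion sentence is wider than that.

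The size of the gain is uncertain: 9% to 49% of residual variance for an assumed r of 0.3 to 0.7, with the upper end the most favourable case. The documents give no correlation, no prevalence or severity of prior pain, no VAS standard deviation and no relevant VAS difference, so every pain figure above is illustrative.

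**What to change.** 1. Add a week-0 VAS for elbow and shoulder to Table 1, taken at consent, before reduction and before the envelope is opened.
2. Compare the arms on elbow and shoulder VAS by ANCOVA, with the joint's own week-0 value as covariate, and report the week-0 values with the baseline data.
3. Limit the Discussion sentence to the difference between above- and below-elbow immobilization. The week-0 score would not justify the wider wording, since it reflects injury-related as well as prior pain and no arm is unsplinted.

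The cost is one short form at enrolment, one covariate in the analysis and one reworded sentence. Patients already enrolled will lack the score, so the plan should say how a missing covariate is handled and keep them in the intention-to-treat comparison.

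### The article says randomization will equalise the groups and names only unadjusted between-group tests, although it calls age prognostic itself

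*Protocol article*

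**What the plan says.** Three statements in the protocol article belong together.

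- **Discussion.** Adults of all ages are enrolled, and "it is known that the DRF in the elderly has different behavior and prognosis when compared to the young". The next sentence answers this with: "Randomization will equalize the distribution homogeneously between the groups, allowing the sample to be faithful to the population".
- **Statistical methods, baseline.** "As a method to confirm the effectiveness of the randomization, baseline data will be compared in the two groups of comparison". The section does not name the form of this comparison and attaches no consequence to its result.
- **Statistical methods, between-group tests.** "For comparison between proportions, we will consider Pearson’s chi-square test"; continuous data get Student's t test. No covariate is mentioned for either.

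The Randomization and masking section describes software-generated assignment with numbered opaque envelopes, opened in the operating room once reducibility is verified. It mentions no stratification or minimisation.

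**The concern.** The article names a prognostic factor and then sets it aside because randomization will make the groups alike. That reasoning fails twice. Randomization guarantees balance on average over repeated allocations, not in the one trial that is run. And whether a sample reflects the population depends on who is enrolled, not on how they are allocated.

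The baseline comparison does not repair this. After concealed allocation, any difference between the arms is chance, so the comparison cannot confirm that randomization worked. As nothing follows from it, it does not protect the treatment estimate either.

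At stake is how closely the treatment effect is estimated, and how exposed it is to a chance difference in age. Without a prespecified covariate, a visible age imbalance would also invite a decision on adjustment after the data have been seen.

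**Working it through.** **Inputs from the documents.** DASH difference and SD: "scores are greater than 10 points and standard deviation 15 points" (Sample size calculation). Two-sided test: "We considered the test as bicaudal". Significance level: "We will consider as significant when alpha < 0,05". Evaluable n is 58 per group, and the target is 64 per group.

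**Assumptions.** Simple randomization with 64 per arm. The share of DASH variance explained by covariates (R²) is not given, so 0.05 to 0.30 is shown.

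**1. The plan's own figure.** The article states: "To detect this difference (Student T-test) and statistical power of 95% resulted in a 58 patient sample size per group".
- n = 2 × (1.960 + 1.645)² × (15/10)² = 58.5, that is 59 per group. An exact t-test calculation gives 59.5, that is 60.
- Power at 58 per group is 94.8% (normal approximation) or 94.5% (exact t).
- 58 × 1.10 = 63.8, that is 64.

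The stated size reproduces to within rounding and is not in dispute.

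**2. How equal the groups will be.** For a binary factor, the counts in the two arms are independent binomials with n = 64.

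| Prevalence | Differs by ≥10 points | Differs by ≥15 points | Exactly equal |
|---|---|---|---|
| 50% | 25% | 9% | 7% |
| 30% | 21% | 7% | 8% |

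For a continuous factor such as age, the standardised difference has standard error √(2/64) = 0.177. It reaches 0.2 in 26% of trials and 0.3 in 9%.

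**3. What a baseline comparison can show.** If it were done by independent tests at 5%, correct randomization would still give at least one significant result with probability 1 − 0.95^k: 14% for 3 tests, 23% for 5 and 40% for 10.

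**4. Effect of an imbalance on the unadjusted DASH comparison.** The shift is √R² × d × 15, where d is the imbalance in SD units. The unadjusted standard error is 15 × √(2/58) = 2.79. Given the imbalance, the spread is 2.79 × √(1 − R²).
- d = 0.3, R² = 0.10: shift 0.316 × 0.3 × 15 = 1.4 points; conditional type I error 6.8%.
- d = 0.3, R² = 0.30: shift 0.548 × 0.3 × 15 = 2.5 points; conditional type I error 10.0%.
- d = 0.2, R² = 0.10 to 0.30: shift 0.9 to 1.6 points; conditional type I error about 5.2%.

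Averaged over all randomizations the type I error is 5%.

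**5. What adjustment buys for DASH.** Residual SD = 15 × √(1 − R²); half-width = 1.96 × SD × √(2/58).

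| R² (assumed) | Residual SD | 95% CI half-width | Power at 58 per group | n per group for 95% power |
|---|---|---|---|---|
| 0 (as planned) | 15.0 | 5.5 | 94.8% | 59 |
| 0.05 | 14.6 | 5.3 | 95.8% | 56 |
| 0.10 | 14.2 | 5.2 | 96.6% | 53 |
| 0.20 | 13.4 | 4.9 | 98.0% | 47 |
| 0.30 | 12.5 | 4.6 | 99.0% | 41 |

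**The case against.** The strongest reply is that no validity error exists. An unadjusted comparison in a randomized trial is valid, and its ordinary confidence interval already covers chance imbalance. Covariate adjustment is a matter of efficiency that is often left to the analysis plan, which is not shown. The equalisation sentence is Discussion prose, and DASH is already planned at 95% power. All of this stands, and it limits the size of the point. It does not remove the point: the article states a wrong reason for not worrying about age, and the between-group tests it names are unadjusted.

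Four stronger readings are tempting, and the documents do not support them.

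- A reader might infer that the planned tests are biased or inflate the type I error. They do so only conditionally on a sizeable imbalance, not over all randomizations.
- A reader might infer that AO type and initial displacement are recognised prognostic factors left unadjusted. The article gives a prognostic role to age alone; the other two appear as entry criteria. It also gives no rates of lost reduction by fracture type, so no shift in that outcome can be worked out.
- A reader might infer that baseline significance tests are planned. The text says only that baseline data will be compared, so step 3 of the working applies only if tests are used.
- A reader might infer that allocation is certainly unstratified. A condensed article may omit this, and the omission is not counted here.

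**Conclusion.** The point holds as a modest, nearly free improvement and a correction of wording. The equalisation and representativeness claims are wrong as written, and a baseline comparison cannot confirm randomization. The named tests are valid, but they forgo some precision and some protection against chance imbalance in a factor the article itself calls prognostic.

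For DASH the gain is small: with assumed R² of 0.10 to 0.30, the half-width falls from 5.5 points to between 5.2 and 4.6, and power rises from 94.8% to between 96.6% and 99.0%. Age alone may explain less than this range. No DASH is taken before immobilization begins, so a baseline score is not available to raise R². For maintenance of reduction the gain cannot be sized, because the sample size calculation covers DASH only and the article gives no expected rate. The imbalance probabilities assume simple randomization; stratification by age, if the full protocol has it, would lower them for age.

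**What to change.** - **Analysis.** Prespecify age as a covariate in the primary between-group comparisons: a linear model for DASH, and logistic regression with a marginal risk difference for maintenance of reduction. AO group and initial displacement are established at entry and may be added if the team judges them prognostic, provided the list is fixed before unblinding. Nothing here calls for adjusting complications, where events may be few, or for adding institution.
- **Baseline data.** Present them descriptively by arm, and drop the purpose of confirming randomization.
- **Discussion.** Say that randomization balances the groups in expectation and that remaining differences are due to chance. Remove the claim that it makes the sample representative.

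The cost is a change of wording and slightly more analysis work. Patient numbers, visits and measurements stay as they are.
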